### Secondary hypotheses

Participants in the verum TPS group or the sham TPS group will have < 5% somatic discomfort during the 2-week TPS intervention on young adolescents with ADHD.Participants in the verum TPS group will have a 30% improvement in ADHD symptoms and behavior compared with the sham TPS group after 2 weeks of TPS treatment and be maintained at the 1- and 3-month follow-ups.Participants in the verum TPS group will have a 30% improvement in executive function after 2 weeks of TPS treatment compared with the sham TPS group and be maintained at the 1- and 3-month follow-ups.Participants in the verum TPS group will have a 30% improvement in both attention deficit and reduction in hyperactivity and impulsivity after 2 weeks of TPS treatment compared with the sham TPS group, and be maintained at the 1- and 3-month follow-ups.Participants in the verum TPS group will have more brain connectivity changes after 2 weeks of TPS compared with the sham TPS group and be maintained at the 1- and 3-month follow-ups.

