### Neuroimaging

Participants will receive pre- and post-treatment MRI scans (total: two MRI scans) to measure any changes in structural and functional connectivity changes in the brain. Structural MRI, DTI, and rs-fMRI will be performed using a 3T scanner at the UBSN (ZB216), The Hong Kong Polytechnic University. The subjects will be closely monitored by the research assistant and the radiographer during scanning. The whole scan will last around 30 min including preparation. Structural MRI scans including T1 sequences will be used for assessing regional volume differences across the whole brain. High-resolution sagittal 3D T1-weighted (SPGR/MPRAGE) images of 1 × 1 × 1 mm will be acquired with a repetition time (TR) = 1,820 ms, echo time (TE) = 3.75 ms, inversion time (TI) = 1,100 ms, and flip angle = 70°. DTI sequence will be conducted using single-shot spin-echo echo-planar imaging, with diffusion-sensitizing gradients applied along 16 non-collinear directions with diffusion weighting factor b = 1,000 s/mm^2^, plus two b = 0 images. The imaging parameters will be TR/TE = 1,200/82 ms, matrix size = 128 × 128, the field of view (FOV) = 240 mm, slice thickness = 3 mm with no intersection gap, number of excitations = 2, and number of slices = 67. Finally, resting-state fMRI of 150 T2-weighted gradient echo planar imaging (EPI) will be acquired with TR = 2 s and TE = 32 ms; 32 slices, with a resolution of 3 × 3 × 4 mm, during which subjects will view a fixation cross (“+”) passively at the center of the screen. Images processing and analysis will be performed using software packages including FSL (http://fsl.fmrib.ox.ac.uk/fsl/fslwiki/). Total brain and total gray and white matter volumes will be extracted from the T1 structural scan. Gray matter and white matter tissue maps will be segmented and compared for regional tissue density differences using voxel-based morphometry (VBM) (53). Structural connectivity will be assessed by fractional anisotropy (FA) maps extracted from DTI imaging.

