### Statistical analyses

All statistical analyses will be performed using the statistical software R for Windows (R version 4.1.0). Means and standard deviations (SD) for the continuous variables will be presented, while numbers and percentages for the categorical variables will be shown. A *p*-value of < 0.05 is considered statistically significant. Sociodemographic differences between the TPS group and the sham TPS group will be analyzed using the Chi-square test and *t*-test. If there are significant differences between sociodemographic factors, covariates will be considered confounding variables in the analyses. The normality of the primary outcome (SNAP-IV) scores will be tested by the Shapiro–Wilk test for each combination of factor levels (group and time). *T*-test will be used to test the baseline difference. A linear mixed model will be used to test the group (between-subject factor), time (within-subject factor), and group × time interaction effects of the SNAP-IV score between the TPS group and the sham TPS group. *Post-hoc* comparisons between groups and time points will be conducted using a *t*-test with Bonferroni correction. The normality of the secondary outcome scores will be tested by the Shapiro–Wilk test for each time point. For normally distributed outcomes, a linear mixed model will be used to determine whether the outcome scores are significantly different between the pre- and post-tests. For outcome scores that deviate grossly from normality, a non-parametric Friedman test will be used to test the mean difference. A Cohen's *d* effect size for each outcome will be calculated, where *d* = 0.2, 0.5, and 0.8 correspond to small, medium, and large effect sizes (54). Missing data will be managed by multiple imputations (55). For the neurological rs-fMRI data, a longitudinal voxel-based morphometry (VBM) will be used to examine whether TPS produces local changes in gray matter. Specifically, relative local increases and decreases between pre- and post-intervention scans will be compared within and between study groups. The diffusion MR data will be analyzed using the diffusion tensor model (56). Two standard diffusion indices will then be obtained: the apparent diffusion coefficient and the fractional anisotropy. Pre- and post-treatment DTI scans will permit the assessment of changes in axial diffusivity, with lower values being interpreted as the structural enhancement of white matter.

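### Lower axial diffusivity is pre-set as white-matter enhancement, although it is not a listed index and can fall together with FA, the protocol's own measure of structural connectivity

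*Protocol article*

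**What the plan says.** Three statements in the protocol article bear on how the diffusion data will be read.

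- Neuroimaging: "Structural connectivity will be assessed by fractional anisotropy (FA) maps extracted from DTI imaging". No direction is given for FA.
- Statistical analyses: "The diffusion MR data will be analyzed using the diffusion tensor model", followed by "Two standard diffusion indices will then be obtained: the apparent diffusion coefficient and the fractional anisotropy".
- Statistical analyses, next sentence: the scans before and after treatment are to be used to assess how AD changes, "with lower values being interpreted as the structural enhancement of white matter".

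The imaging hypothesis, under Secondary hypotheses, is that the verum group "will have more brain connectivity changes after 2 weeks of TPS compared with the sham TPS group". It names no index and no direction.

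**The concern.** AD is not one of the two indices that the same section has just listed, yet it is the only diffusion quantity given a meaning. FA, which the Neuroimaging section uses to assess structural connectivity, is given none.

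The rule also reads AD on its own, with no reference to FA or RD. AD is one component of FA, and in the tensor model FA moves in the same direction as AD when the other eigenvalues stay put. A change that the AD sentence calls enhancement can therefore coincide with a decline in the index chosen for structural connectivity.

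At stake is one conclusion of the imaging analysis: a claim of white-matter enhancement after TPS that the protocol's own connectivity measure would not support.

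**Working it through.** The protocol gives no figure to reproduce here and no diffusion values. All eigenvalues below are assumptions, in units of 10⁻³ mm²/s. The sign of the result does not depend on them.

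**Definitions.** For eigenvalues L1 ≥ L2 ≥ L3 > 0, AD = L1, and RD is the mean of L2 and L3. With T = L1 + L2 + L3 and S = L1² + L2² + L3²,

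FA² = (3/2)(1 − T²/(3S)).

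**Sign when AD alone changes.**

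d(T²/S)/dL1 = (2T/S²)(L2² + L3² − L1·L2 − L1·L3) = (2T/S²)[L2(L2 − L1) + L3(L3 − L1)].

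Both terms in the bracket are zero or negative, and at least one is negative unless all three eigenvalues are equal. T²/S therefore falls as L1 rises, so FA rises with AD and falls when AD alone falls. A numerical check on 200,000 random tensors, lowering only AD and keeping it the largest eigenvalue, found no case in which FA failed to fall.

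**Size, 10% fall in AD with the other eigenvalues fixed.**

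| Assumed eigenvalues | FA before | FA after | Change |
|---|---|---|---|
| 1.7, 0.3, 0.3 | 0.799 | 0.775 | −0.024 |
| 1.4, 0.5, 0.4 | 0.620 | 0.576 | −0.044 |
| 1.2, 0.6, 0.5 | 0.458 | 0.403 | −0.055 |
| 1.0, 0.7, 0.6 | 0.265 | 0.205 | −0.060 |

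**A larger illustrative fall.** With L2 = L3 = RD, the formula reduces to FA = (AD − RD)/√(AD² + 2RD²). Let AD go from 1.7 to 1.3, a fall of 0.4/1.7 = 24%, with RD = 0.4:

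- before: 1.3/√(2.89 + 0.32) = 0.726
- after: 0.9/√(1.69 + 0.32) = 0.635

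For RD of 0.3, 0.5 and 0.6, FA goes from 0.799 to 0.731, 0.652 to 0.541 and 0.579 to 0.451. Over RD from 0.3 to 0.6 the loss is thus 0.07 to 0.13.

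**When the conflict disappears.** Put r = RD/AD in the same formula: FA = (1 − r)/√(1 + 2r²), which decreases as r rises from 0 to 1. FA therefore falls exactly when AD falls by a larger percentage than RD. Starting from (1.4, 0.5, 0.4), where FA is 0.620, and lowering AD by 10%:

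| Fall in both radial eigenvalues | FA after | Direction |
|---|---|---|
| 0% | 0.576 | falls |
| 5% | 0.598 | falls |
| 10% | 0.620 | unchanged |
| 15% | 0.642 | rises |

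The AD rule gives the same answer, enhancement, in all four rows. FA gives three different answers.

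**The case against.** The strongest reply is that the document contains no written contradiction. It never says that higher FA is better; the only direction on the page is the one for AD. The formula shows that FA falls, not that a fall is bad. That is correct. Taking higher FA as stronger structural connectivity is the natural reading of an index chosen to assess it, but it remains a reading.

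Two further points also stand. Lower AD and higher FA can occur together, when RD falls by a larger percentage. And the 24% example is only illustrative: nothing in the protocol suggests a change of that size, or with RD fixed, over a two-week treatment.

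A reader might infer that the same change is bound to be reported in opposite directions, or that the imaging objective fails. The documents do not support either. Only one direction is defined, and the conflict is conditional. The third objective concerns functional connectivity, which is analysed by resting-state fMRI, and the connectivity hypothesis speaks of more changes without saying which way. Nor is it shown that any result could be claimed as benefit: fixing a direction in advance restricts the reading of that one index.

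It can also be said that an article need not list every index, that AD comes from the same tensor fit, and that a joint rule across indices belongs in the full protocol or SAP. The absence of such detail is not the point here. The article states an interpretive rule, and that rule applied as written can give a conclusion that the named connectivity index does not bear out.

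**Conclusion.** The point holds in a limited form. The article commits in advance to calling lower AD an enhancement, attaches that reading to a quantity outside its own list of two, and does not tie it to FA. Where AD falls by a larger percentage than RD, the rule declares enhancement while FA falls. For a 10% fall in AD alone the drop in FA is 0.02 to 0.06 across the assumed tensors; it is zero when RD falls by the same percentage, and FA rises when RD falls by more.

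The conclusion rests on the tensor definition of FA, which is exact, and on the unwritten reading that higher FA means stronger structural connectivity. The sizes rest on assumed eigenvalues.

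The point bears on the structural-connectivity part of the imaging analysis only. Randomization, sample size, safety and the SNAP-IV analysis are untouched. Severity: minor.

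**What to change.** In the Statistical analyses section:

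1. Delete the stand-alone reading of lower AD as enhancement.
2. State that DTI structural connectivity will be judged on the verum-minus-sham difference in pre-to-post change in FA, in line with the Neuroimaging section, and write down in advance which direction of FA change will be read as stronger connectivity. Without that direction, the edit would leave the DTI analysis with no stated reading at all.
3. Add AD and RD to the list of indices, and report them and ADC descriptively beside FA, without a benefit direction.

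This takes one or two sentences. It needs no new scan, because FA is already planned and AD and RD come from the same tensor fit. It should be settled before the DTI data are analysed. The small downside is giving up one directional claim.

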## Discussion

This study is the first RCT to evaluate the efficacy and safety of TPS in patients with ADHD nationwide. Findings that emerge from this project will have a significant impact on patients/caregivers and the community at large. Findings will inform health policymakers on whether TPS could be used as an adjunct treatment in the clinical setting in psychiatry—given the fact that both medications and psychotherapy require long-term input to sustain the therapeutic effects of ADHD. As such, this inevitably increases health costs, the caregiving burden, and the global disease burden. If this project can prove that TPS is effective in the treatment of patients with ADHD, it could instill hope in the patients' families and reduce their psychological burden to a large extent that ADHD is curable and treatable by TPS. This would be a breakthrough in neuroscience research specific for adolescents with special education needs (SEN) in Hong Kong.

## Trial status

This trial was registered with clinicaltrails.gov on 10 August 2022 (protocol version). Recruitment commenced from 1 June 2022 to 30 Sept 2022.

## Ethics statement

The studies involving human participants were reviewed and approved by Human Subjects Ethics Sub-Committee, The Hong Kong Polytechnic University. Written informed consent to participate in this study was provided by the participants' legal guardian/next of kin.
